### **8.1.3 Other study parameters (if applicable)**

Not applicable

## **8.2 Randomisation, blinding and treatment allocation**

When parents/caretakers provide informed consent, the child will be randomly assigned (1:1) to the intervention (laparoscopic repair) or control group (open repair) using a web-based application with a computer-generated list with random block sizes of four or six and rendered by an independent data manager. The block size of the randomisation scheme is unknown to the study personnel. Participants and investigators are aware of allocation; masking is impossible because of the nature of the intervention.

### **8.3 Study procedures**

General anaesthesia will be given to all patients undergoing hernia repair. We expect that duration of hospitalization will be similar in both groups, but this is also part of the research questions. Duration of surgery for the laparoscopic technique is expected to be shorter than the open repair group, this is one of the secondary objectives of this study. Different surgical instruments will be used during surgery (i.e. telescope, trocars and 18 gauge needle for the laparoscopic procedure). If a disorder of sexual development is found during surgery, the patient will be referred to a paediatrician for further analysis and/or treatment. The children will not be excluded from the study since a disorder of sexual development does not affect our outcome measures or causes extra hazard for the patient.

#### Assessment of study parameters/endpoints

The following applies to all infants admitted to the hospital for inguinal hernia repair included in this study.

Preoperative size of both testes, the number of operations per infant, length of hospital stay, total duration of operations (including anaesthesia) and perioperative complications of surgery (iatrogenic injury, apnoea) will be recorded in Case Report Forms by the (fellow) paediatric surgeon. One telephone call is performed by a member of the research team after four weeks in the control and intervention group to obtain information regarding recovery of the patient, wound healing and recurrence. Pre-operative and four weeks and one year post-operative, parents or patients older than 12 years of age (with the aid of their parents) will fill out an online questionnaire regarding health of the subject and cost-effectiveness. Invitations for the questionnaires will be sent by Castor EDC, in which the results also will be recorded (13). Furthermore one and two years after surgery telephone call is conducted to assess post-operative complications such as testicular atrophy and recurrence. Prior to the telephone consult, parents are asked to send a photo to the researcher with the help of a secured online application (SURFfilesender) and a coded number

### **8.4 Withdrawal of individual subjects**

Subjects can leave the study at any time for any reason if they wish to do so without any consequences. The investigator can decide to withdraw a subject from the study for urgent medical reasons.

#### **8.4.1 Specific criteria for withdrawal (if applicable)**

Not applicable.

#### **8.5 Replacement of individual subjects after withdrawal**

After withdrawal patients will not be replaced.

#### **8.6 Follow-up of subjects withdrawn from treatment**

Patients withdrawn from treatment will be asked to give permission for a telephone consult one year after surgery to investigate the endpoints of the study.

#### **8.7 Premature termination of the study**

The study will be terminated premature if new evidence has arisen that conclude that the effect of the treatment arm is inferior and it is therefore not ethical to continue treatment of more patients with this inferior arm.

In case the study is ended prematurely, the sponsor will notify the accredited METC within 15 days, including the reasons for the premature termination.

### **9. SAFETY REPORTING**

#### **9.1 Temporary halt for reasons of subject safety**

In accordance to section 10, subsection 4, of the WMO, the sponsor will suspend the study if there is sufficient ground that continuation of the study will jeopardise subject health or safety. The sponsor will notify the accredited METC without undue delay of a temporary halt including the reason for such an action. The study will be suspended pending a further positive decision by the accredited METC. The investigator will take care that all subjects are kept informed.

#### **9.2 AEs, SAEs and SUSARs**

##### **9.2.1 Adverse events (AEs)**

Adverse events are defined as any undesirable experience occurring to a subject during the study whether or not considered related to the experimental intervention. Adverse events will be recorded from the start of the study until the moment of first follow-up (at 4 weeks), since adverse events do not occur after a maximum of four weeks after the intervention. All adverse events, within four weeks post-operative, reported spontaneously by the subject or observed by the investigator or his staff will be recorded.

### **9.2.2 Serious adverse events (SAEs)**

A serious adverse event is any untoward medical occurrence or effect that

- results in death;
- is life threatening (at the time of the event);
- requires hospitalisation or prolongation of existing inpatients' hospitalisation;
- results in persistent or significant disability or incapacity;
- is a congenital anomaly or birth defect; or
- any other important medical event that did not result in any of the outcomes listed above due to medical or surgical intervention but could have been based upon appropriate judgement by the investigator.

An elective hospital admission will not be considered as a serious adverse event. Serious adverse events will be recorded and reported throughout the first four post-operative weeks of the study, since adverse events do not occur after a maximum of four weeks after the intervention.

If a life threatening SAE is encountered, this study will be delayed immediately, since inguinal hernia repair is surgery accompanied by minimal complications. The safety committee is then asked to perform and report an analysis of this SAE before the study will continue

The investigator will report all SAEs to the sponsor without undue delay after obtaining knowledge of the events.

The sponsor will report the SAEs through the web portal *ToetsingOnline* to the accredited METC that approved the protocol, within 7 days of first knowledge for SAEs that result in death or are life threatening followed by a period of maximum of 8 days to complete the initial preliminary report. All other SAEs will be reported within a period of maximum 15 days after the sponsor has first knowledge of the serious adverse events.

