#### 8.1.2 Secondary study parameters/endpoints (if applicable)

Operative (i.e. injury of spermatic vessels or spermatic cord, tuba lesions, bleeding and apnea) and postoperative complications (i.e. hematoma/scrotal edema, hydrocele, wound infection, iatrogenic ascent of the testis, testicular atrophy and ileus) within one year after primary surgery.

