#### 9.4 Follow-up of adverse events

All AEs that have occurred within the first four post-operative weeks will be followed until they have abated, or until a stable situation has been reached. Depending on the event, follow up may require additional tests or medical procedures as indicated, and/or referral to the general physician or a medical specialist.

SAEs need to be reported till end of study within the Netherlands, as defined in the protocol

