### **12.5 Temporary halt and (prematurely) end of study report**

The investigator/sponsor will notify the accredited METC of the end of the study within a period of 8 weeks. The end of the study is defined as the last patient's last visit.

The sponsor will notify the METC immediately of a temporary halt of the study, including the reason of such an action.

In case the study is ended prematurely, the sponsor will notify the accredited METC within 15 days, including the reasons for the premature termination.

Within one year after the end of the study, the investigator/sponsor will submit a final study report with the results of the study, including any publications/abstracts of the study, to the accredited METC.

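### Sections 9.2.2 and 9.4 set different SAE reporting windows, and the reason given for stopping at four weeks conflicts with the protocol's own one-year complication endpoints

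*Protocol*

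**What the plan says.** Section 9.2.1 defines an adverse event as "any undesirable experience occurring to a subject during the study whether or not considered related to the experimental intervention". It then ends recording at the first follow-up contact, four weeks after surgery, "since adverse events do not occur after a maximum of four weeks after the intervention". Section 9.2.2 gives the same limit and the same reason for serious events: "Serious adverse events will be recorded and reported throughout the first four post-operative weeks of the study".

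Section 9.4 contains two rules. For adverse events in general: "All AEs that have occurred within the first four post-operative weeks will be followed until they have abated" or are stable. For serious events: "SAEs need to be reported till end of study within the Netherlands, as defined in the protocol". Section 12.5 supplies the end point: "The end of the study is defined as the last patient's last visit". Sections 3 and 8.3 plan contacts with the families one and two years after surgery.

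Other sections look well past four weeks. Section 8.1.2 makes complications a secondary endpoint, among them "iatrogenic ascent of the testis, testicular atrophy and ileus) within one year after primary surgery". The calls in section 8.3 are meant to find complications such as testicular atrophy. Section 11.4 gives, as the risk for control children, a later contralateral hernia that may incarcerate.

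Section 9.5 installs no DSMB, only a safety committee that can be consulted when an SAE occurs. Under section 9.2.2 a life-threatening SAE interrupts the study until that committee has reported, and elective admissions are not SAEs.

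**The concern.** There are two faults in the current text.

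- **Two SAE rules.** One closes recording and reporting at four weeks and the other keeps reporting open to the end of the study. Sites may act differently on the same event, and the monitor, who under section 12.2 checks that (S)AEs are correctly reported, has no single rule to check against.
- **A reason the protocol itself refutes.** The cut-off rests on a factual claim that no adverse events arise after four weeks, yet the protocol plans to count such events for a year and to ask about them at two.

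What is at stake is the speed and route of safety review in a trial in children. The METC deadlines, the halt after a life-threatening event and the safety committee's involvement all start from an SAE. If a serious event after week four is not recorded as one, none of them starts.

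**Working it through.** The protocol gives no figure for late serious events, so the main check sets the sections side by side. A small calculation then sizes the exposure.

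**1. One event under both rules.** Take a child admitted as an emergency at month three with an incarcerated contralateral hernia. Unplanned hospitalisation meets the SAE definition in section 9.2.2.
- Under the window in section 9.2.2, nothing is recorded or reported.
- Under section 9.4, the event is reported, because month three precedes the end of the study. The section 9.2.2 deadlines then apply: to the METC within 7 days if fatal or life-threatening, otherwise within 15.

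**2. The stated reason against the other sections.**
- Section 8.1.2: complications count up to one year. Even its wound-infection definition runs to 30 days, against 28 days for four weeks.
- Section 8.3: calls at one and two years look for complications.
- Section 11.4: incarceration of a later contralateral hernia is foreseen.
- Section 9.2.1: an adverse event is defined by occurrence during the study, which is wider than the window that follows.

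**3. Share of follow-up outside the window.**
- One year: 1 − 28/365 = 0.923, about 92%.
- Two years: 1 − 28/730 = 0.962, about 96%.

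These are shares of calendar time, not of events.

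**4. Exposed incarcerations in the first year.** Inputs from section 4.4: 422 evaluable children, so 211 per arm (6% versus 1%, two-sided 0.05, power 0.80, pooled chi-square without continuity correction reproduces 211 and 422). The rates of metachronous contralateral inguinal hernia (MCIH) are 6% open and 1% PIRS, taken as one-year rates. Input from section 1: 3-16% of children with inguinal hernia have incarceration. That this range applies to MCIH is an assumption; the protocol does not say so.

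Expected incarcerations = n × MCIH rate × incarceration share.

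| Arm | MCIH | at 3% | at 16% |
|---|---|---|---|
| Open | 211 × 0.06 = 12.7 | 12.7 × 0.03 = 0.4 | 12.7 × 0.16 = 2.0 |
| PIRS | 211 × 0.01 = 2.1 | 2.1 × 0.03 = 0.1 | 2.1 × 0.16 = 0.3 |

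Any that fall within the first four weeks are caught under either rule, so these are upper figures for incarceration on the stated assumptions. They do not cover other late serious events. The definition in section 9.2.1 includes unrelated events, and the protocol gives no rate for those.

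**The case against.** **The two rules might be reconciled by reading.** The closing words of the section 9.4 sentence could point back to the four-week limit, or, given that section's title, the sentence could mean only that SAEs which began within four weeks are reported on until the end. Neither reading is impossible. But the preceding sentence in section 9.4 does limit itself to events with onset in four weeks and the SAE sentence does not, and the natural referent of its closing words is the end of study, which section 12.5 defines. A reporting rule that needs this much interpretation should be rewritten in any case.

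**A reader might infer that the safety comparison between the arms is cut short.** The documents do not support this. Recurrence or MCIH requiring reoperation is the primary endpoint (section 8.1.1), complications to one year are a secondary endpoint (section 8.1.2), and sections 10.1 and 10.2 compare them between arms. That comparison does not depend on AE or SAE forms.

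**A reader might infer that about 13 open-arm and 2 PIRS-arm events go unreported.** Those are expected MCIH cases. Elective repairs are not SAEs under either rule, so only unplanned presentations are exposed. Nor does the protocol predict an arm difference in late events other than MCIH and what follows from it.

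**A reader might infer that the committees would never learn of late events.** That goes too far. If section 9.4 governs, late SAEs are reported. The METC also receives a yearly progress report covering serious events and other problems (section 12.4), the monitor reviews primary endpoints (section 12.2), and the sponsor's duty to suspend in section 9.1 has no time limit. None of these replaces expedited reporting, and the yearly report can list only the SAEs that were recorded.

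What stands against these objections is the conflict itself and the unsupported reason for the cut-off.

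**Conclusion.** The point holds as an internal contradiction with a safety-reporting consequence. Sections 9.2.2 and 9.4 cannot both be followed, and the reason given for four weeks is inconsistent with sections 8.1.2, 8.3 and 11.4.

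The consequence is conditional. Only if section 9.2.2 governs does a late unplanned SAE miss expedited METC reporting, the halt for life-threatening events and safety committee review, with no DSMB behind them. For incarcerated contralateral hernia this concerns about zero to two children in the open arm and fewer than one in the PIRS arm in the first year. That rests on the planning rates in section 4.4 being one-year rates and on the assumed transfer of the 3-16% range. The small count does not make the fault harmless, since under section 9.2.2 a single life-threatening event is enough to interrupt the trial.

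The primary endpoint, the sample size and the planned comparison of complications are unaffected.

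**What to change.** - Delete, in sections 9.2.1 and 9.2.2, the statement that adverse events do not arise after four weeks.
- Reconcile sections 9.2.1, 9.2.2 and 9.4 to one SAE window, consistent with the end-of-study reporting duty that section 9.4 already states. Because section 12.5 defines that end for the trial and not for each child, say what applies to a child whose own two-year call has passed.
- State that sites report an SAE when they learn of it, and add a question on serious events to the planned one- and two-year calls. The calls alone would not be enough, since an event at week six might surface only at one year.
- Late non-serious complications can stay as endpoint data under section 8.1.2, with the text saying so. Recording each of them again as an adverse event would largely duplicate those data.

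The cost is a wording amendment, notified to the METC under section 12.3, and a few extra SAE forms. No new visits are needed.

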#### 9.5 Safety Committee

Both treatment strategies (laparoscopic (intervention) and open (control) hernia repair) are currently performed in children with inguinal hernia who need to undergo repair. Consequently, there are no additional risks for subjects of this study and it is therefore not necessary to install a DSMB. Because this study is undertaken in children, the investigators do want to install a safety committee, which can be asked for help if a SAE is encountered.

The committee will be formed by a paediatric surgeon ([REDACTED]), [REDACTED], [REDACTED], [REDACTED], a surgeon with expertise in hernia repair ([REDACTED]), [REDACTED], and a paediatrician ([REDACTED]).

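### Minor: the automatic pause in section 9.2.2 names only life-threatening SAEs, although the same section lists death separately and names both in its 7-day reporting rule

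*Protocol*

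**What the plan says.** Section 9.2.2 of the Protocol defines an SAE by six criteria. The first is "results in death". The second, listed separately, is "is life threatening (at the time of the event".

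The section then sets two rules for the gravest events:

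- **Pause.** "If a life threatening SAE is encountered, this study will be delayed immediately". The reason given is that this operation has few complications. The next sentence adds the restart condition: "The safety committee is then asked to perform and report an analysis of this SAE before the study will continue".
- **Expedited reporting.** The sponsor reports to the METC "within 7 days of first knowledge for SAEs that result in death or are life threatening".

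Two other sections bear on what happens after a serious event. Under section 9.1, "the sponsor will suspend the study if there is sufficient ground that continuation of the study will jeopardise subject health or safety", and then: "The study will be suspended pending a further positive decision by the accredited METC". Section 9.5 explains that no DSMB is installed and sets up a safety committee "which can be asked for help if a SAE is encountered".

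**The concern.** The two rules in section 9.2.2 have different triggers. Reporting covers death and life-threatening events; the pause covers only the latter. If the section's own categories are applied literally, a child who survives a life-threatening event stops the trial automatically, whereas a death not classed as life threatening when the event occurred does not. The sponsor's stated reason for pausing, that serious harm is not expected from this operation, applies at least as strongly to a death.

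What is at stake is the conduct of the trial in the days after such a death: whether further children are operated on within the study while the event is reviewed. The study plans to randomise 464 children without a DSMB, and this pause is the only safety stop in the document that takes effect without someone first weighing the evidence. Its trigger should not depend on which box a fatal event was recorded under.

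**Working it through.** No arithmetic applies beyond a count, so the check compares the provisions.

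**Step 1: the categories in section 9.2.2.** Of the six SAE criteria, two (death; life threatening) carry the 7-day reporting deadline. Of those two, one (life threatening) is named in the pause.

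**Step 2: does life threatening already include death here?** Three features of the section make that unsafe to assume.

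- The criteria list gives the two separately.
- The reporting rule names both again, which would be redundant if one contained the other.
- The second criterion is judged at the time of the event, so it does not refer to the later outcome.

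Against this, the criteria are not mutually exclusive. One event can meet both, and most fatal events would.

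**Step 3: the committee analysis.** The restart sentence refers back to the event that caused the pause. The required analysis therefore has the same trigger and the same gap.

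**Step 4: does another section pause the study after a death?**

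| Section | What it provides | Automatic after a death? |
|---|---|---|
| 8.7 Premature termination | Ends the study on new evidence that one arm is inferior | No |
| 9.1 Temporary halt | Suspension is obligatory, but only once there is sufficient ground of jeopardy | No; needs a judgement |
| 9.2.2 Reporting rule | Report to the METC within 7 days | Report yes, pause no |
| 9.5 Safety Committee | Committee may be consulted on any SAE | No; optional and pauses nothing |
| 12.5 Temporary halt and end of study | Notification once a halt or end has occurred | No |

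**Step 5: what is left.** The uncovered case is a death recorded under the first criterion and not under the second. A hypothetical example is an unwitnessed death at home, where nobody assessed the event as it happened. The document gives no mortality figure, so no frequency can be attached to this. Deaths should be very rare after this elective operation, and deaths falling outside the second criterion rarer still.

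**The case against.** The strongest reply is that an event that kills a child is, in ordinary language, life threatening. The words about the time of the event most naturally separate actual danger from danger that might have developed; nothing says that they remove fatal events. The reason given for the pause points the same way. On this view the sentence is loosely worded and deaths were never meant to be left out. In addition, a death must be reported to the METC within 7 days. If the sponsor suspends under section 9.1, restart needs a positive METC decision, which is a stricter condition than the committee analysis in section 9.2.2.

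Most of this stands. It shows that the omission is probably unintended, that it would seldom matter, and that a sensible sponsor would probably suspend after a death anyway. It does not make the two sentences of section 9.2.2 agree, and it does not turn the section 9.1 judgement into an automatic pause.

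A reader might go further and infer that deaths in general do not stop this trial, or that the sponsor chose to exempt them. The documents do not support either inference. Nearly all fatal events would meet the life-threatening criterion and so trigger the pause, the remainder still fall under sections 9.1, 9.2.2 (reporting) and 9.5, and nothing states an intention to exempt deaths.

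**Conclusion.** The point holds as a minor inconsistency of low severity. The trigger for the pause in section 9.2.2 is narrower than the reporting rule beside it and narrower than its own rationale. Read literally, it leaves a death recorded only under the death criterion without an automatic pause and without a required committee analysis.

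The conclusion rests on two assumptions: that staff apply the criteria as the section lists them, and that an occasional death might be recorded under the first criterion alone. If every death were also classed as life threatening, the gap would vanish in practice and only the uneven wording would remain. There is no numerical effect, and no endpoint, estimate, error rate or sample size changes. The reason to act is the gravity of the event and the ease of the correction, not its likely frequency.

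**What to change.** In section 9.2.2, change the trigger of the pause from a life-threatening SAE to *an SAE that results in death or is life threatening*, and leave the rest of the sentence and the committee requirement as they are. The trigger then matches the 7-day reporting rule in the same section. Section 9.1 needs no change: it already states its halt criterion and the METC decision needed to restart.

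The cost is one phrase in a protocol amendment notified to the METC, with no new procedures or staff. The only downside is that a death clearly unrelated to surgery would also cause a short pause while the committee reviews it.
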